**Fig 1 pone.0321811.g001:**
[figure not shown]
SPIRIT Schedule Enrollment.

#### Procedures *during the* treatment period.

At weeks 2, 6, and 10 (±3 days), patients will be contacted by telephone to assess their adherence to the dietary supplement using the MARS-5 test and to monitor safety (Appendix 2 in S2 File). All symptoms reported by patients will be further assessed by a specialist in internal medicine and shall assess the intensity of an AA/unwanted effect and record it in the CCL, based on three intensity and relationship levels: mild, moderate and severe/ probable, possible and unrelated. All detected effects shall be reported to the health personnel for the correct follow-up of the patient. If any patients are identified as non-adherent during these intermediate check-ins, the significance of maintaining adherence will be emphasized to maximize health outcomes. Additionally, patients will receive biweekly calls (at weeks 2, 4, 6, 8, and 10 ± 3 days) to monitor their telerehabilitation treatment, during which the intensity and level of exercises will be reviewed and adjusted as necessary (Fig 2).

### Intervention

The treatment will take place for 12 weeks and will include both nutritional supplement and telerehabilitation. Participants must complete a therapeutic exercise programme five days a week via HEFORA telerehabilitation platform, which can be accessed at www.hefora.net or through the mobile app (HEFORA, Fisio Consultores, Zaragoza, Spain). The rehabilitation program will be designed following the recommendations of the NICE guideline [21,22] and the European and American Thoracic Societies [22]. It will include aerobics, strength and pulmonary rehabilitation, structured into three levels of difficulty, each featuring different exercises, except for [23] the pulmonary exercises (Appendix 1 in S1 File). Participants will be categorized into levels based on their fatigue measured with the FSS scores: those scoring 6.00 or higher will be in the first level, those with scores between 5.00 and 5.99 in the second, and those scoring between 4.00 and 4.99 in the third. Each participant will begin with 10 minutes of the prescribed aerobic exercises and three sets of strength exercises, performing as many repetitions as they can manage. The pulmonary exercises will remain consistent throughout the intervention, consisting of 2 sets of 10 repetitions each, with a target fatigue level of less than 3 on the Borg Scale.

For the first two weeks, all participants will perform the exercises with a fatigue intensity ranging between 3.00 and 4.00. After two weeks, this intensity will be increased to a range of 5–7. Progression in the exercise program will be assessed every two weeks during control calls. If any symptoms worsen, the participant’s progression in the program will be paused until the next assessment.

### Nutritional Intervention

Specialized Pro Resolving Mediators (SPMs) (17-HAD, 14-HAD and 18-HEPE) are a natural and standardized nutritional supplement selected to evaluate its efficacy in improving quality of life and other variables in patients with PCC after exposure after 12 weeks. The NG will receive the Nutritional supplement (500mg) enriched in SPMs, administered as 2 capsules after breakfast and 2 capsules after dinner. The Nutritional supplement with SPMs is a commercially available product. It contains an active fraction from fish oil, with standardized amounts of SPMs.

The PG will receive a placebo supplement composed of refined olive oil, gelatin and water which looks exactly like NG. The posology will be equal to the NG.

### Outcome measures

#### Primary outcome: Quality of life: EQ-5D-5L.

The EQ-5D-5L is a generic instrument for measuring health-related quality of life that has been validated [23] in Spanish and in PCC patients. It consists of two components: the levels of severity by dimensions and a visual analogue scale (VAS) on general health. The descriptive system contains five dimensions of health (mobility, self-care, activities of daily living, pain/discomfort, and anxiety/depression) and each of them has five levels of severity (From 1=No problem to 5=unable to perform). Participants indicate their perceived overall health on a VAS from 0 (“worst health I can imagine”) to 100 (“best health I can imagine”). The values obtained will be compared with the reference values [24]. Quality of life will be analyzed as a continuous variable by comparing the relevant statistics according to their distribution at the two points in time and as a qualitative variable by comparing the percentage of patients who improve their scores.

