### Eligibility criteria

All potential participants will be informed before and will have to give their written consent to participate in the study. The inclusion criteria will be: 1) Aged 18–70 years; 2) Diagnostic criteria for having had COVID-19; 3) PCC symptoms for more than 12 weeks, from the end of the acute phase; 4) Fatigue >4 points on the Fatigue Severity Scale (FSS); 5) Independent locomotion. The exclusion criteria will be: 1) Neurological disease preventing them from following the program; 2) Respiratory failure: SaO2 < 90% or respiratory rate ≧30; 3) Rheumatic diseases or acute musculoskeletal injuries that contraindicates exercise; 4) Not daily access to the Internet; 5) Unable to follow oral and written instructions in Spanish; 6) Allergies to fish, shellfish, crustaceans or any of the components of the supplement; 7) Patients who have participated in or completed another clinical trial for the treatment of symptoms derived from COVID-19 in the last 4 weeks; 8) To take immunosuppressive drugs, corticosteroids or non-steroidal anti-inflammatory drugs in the last 2 weeks and 9) Being pregnant. The dropout criteria will be: 1) Pregnancy; 2) At the discretion of the researcher for safety reasons, and/or an adverse event; 3) Non-compliance or lack of adherence to the protocol for more than 2 consecutive weeks.

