#### Statistical analysis.

Statistical analysis will be performed with IBM-SPSS Statistics software version 25 or later. Quantitative variables will be described as mean and standard deviation (SD) if the variable follows a normal distribution or as median and interquartile range for non-normal data. For categorical data absolute and relative frequencies will be computed. The Kolmogorov-Smirnov test will be used to determine the normality of the data. Intra-group variables will be measured with the T-Student test for related samples or the paired samples Wilcoxon test for non-parametric alternative. For inter-group comparations non-parametric analysis will be performed when a non-normal distribution is assumed, using the U Mann Whiney test for comparisons between groups and T-Student test for normal data. Dichotomous variables will be analyzed using the chi-square test. A significant level of 95% will be assumed (p <0.05). If there are more than 15% dropouts, an intention-to treat (ITT) analysis will be performed. Effect size will be calculated using Cohen’s d to determine clinical significance: negligible, small, medium and large differences will be reflected in effect sizes of < 0.2, 0.2–0.5, 0.6–0.8 and > 0.8, respectively.

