## Discussion

Based on our literature review, this is the first study that will combine a dietary supplement based on SPMs with telerehabilitation to reduce the symptoms of patients with PCC. The effectiveness of a nutritional over only a physiotherapeutic intervention would open a field of intervention for these patients who still do not have an effective treatment.

Statistical improvements in quality of life are expected in the Nutritional supplement group to be linked to the improvement of the inflammatory profile although changes are expected in both groups. Specialized nutrition with SPMs might have favorable effects on PCC symptoms due to the potential mechanisms of action for omega-3 acids and their metabolites [25,58]. These actions will result in clinical improvement and therefore in the quality of life perceived by patients. In this regard, Pavlidou’s review confirms that this type of supplementation is beneficial before and during COVID-19 disease and encourages studies like this one to show its effect in patients with PCC [59]. In addition to the nutritional supplement, pulmonary rehabilitation and controlled aerobic and strength training seem to be the most effective interventions used to improve the symptoms of PCC [60]. Furthermore, telerehabilitation has already been shown to be effective in improving quality of life in a similar way to face-to-face treatments, as reported by Dias et al. 2021 in a systematic review [61].

It is expected to have a reduction of long-lasting inflammation in NG for the anti-inflammatory effect of omega-3 [62] by blocking the inflammasome activation and pro-inflammatory cytokine production, thereby restoring tissue homeostasis; improving innate immunity; and reducing oxidative stress by controlling the activity of related enzymes and the generation of free radicals (ROS) [63]. Although the effectiveness of SPMs in reducing inflammation in these patients is not yet proven, in vitro studies show that both Resolvin D1 and Resolvin D2 are potent in reducing the production of pro-inflammatory cytokines, showing the potential role of lipid mediators in the treatment of PCC [64]. The favorable effects of physical exercise on the reduction of inflammation, as well as the modulation of cytokines, have been widely reported in different fields [65,66]. Therefore, improvements can be expected in both groups, although NG will show greater changes, due to the sum of two interventions with anti-inflammatory potential.

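### Continuous EQ-5D-5L is described as a comparison at two time points, and the plan does not say whether its within-arm or its unadjusted between-arm test supports a conclusion about the supplement

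*Protocol article*

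**What the plan says.** The section on the primary outcome gives EQ-5D-5L two analyses. The continuous one is: "Quality of life will be analyzed as a continuous variable by comparing the relevant statistics according to their distribution at the two points in time". The binary one treats quality of life "as a qualitative variable by comparing the percentage of patients who improve their scores". Neither half of the sentence mentions the arms.

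The Statistical analysis section supplies the tests:

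- Within arms: "Intra-group variables will be measured with the T-Student test for related samples or the paired samples Wilcoxon test for non-parametric alternative".
- Between arms, for quantitative variables: the Mann-Whitney test if the data are non-normal "for comparisons between groups and T-Student test for normal data".
- For binary variables: "Dichotomous variables will be analyzed using the chi-square test".

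One threshold, p<0.05, covers all of them. None of the between-arm tests is adjusted for baseline.

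Three other places bear on the point. The aim, at the end of the Introduction, is supplement plus telerehabilitation (NG) against placebo plus the same telerehabilitation (PG). The sample size section powers a PG versus NG comparison of the proportion improving on EQ-5D-5L. The Discussion predicts a benefit in the supplement group "although changes are expected in both groups".

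**The concern.** The trial asks what the supplement adds to rehabilitation. A before/after change in NG mixes the supplement with 12 weeks of exercise, the passage of time and any placebo response. Only the contrast with PG removes those. Yet the one sentence that describes the continuous primary analysis refers to time points, and the paired tests have the same standing as the between-arm tests.

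The risk is that a report sets a significant paired test in NG beside a non-significant one in PG and concludes that the supplement works. That comparison of p-values has a much higher false-positive rate than the between-arm test when the common improvement is modest. When the common improvement is large, the NG test is significant almost always, whether or not the supplement does anything.

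There is also a loss of precision. The baseline EQ-5D-5L is collected from everyone, but the named between-arm tests do not adjust for it.

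**Working it through.** **1. Reproduce the planned size.** Inputs from the sample size section: 30% (PG) and 50% (NG) improving, two-sided alpha 0.05, power 80%, 15% loss.

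n = [1.960·√(2·0.4·0.6) + 0.842·√(0.3·0.7 + 0.5·0.5)]² / 0.20² = 93 per arm. Then 93/0.85 = 109.4, which rounds up to 110.

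The stated 110 per arm is reproduced. The powered analysis is therefore a between-arm comparison of responders, and 93 completers per arm is the planning figure used below.

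**2. Within-arm tests when the supplement does nothing.** The documents give no SD and no expected size of change, so the common improvement d, in units of the SD of change, is assumed over 0.1 to 0.5. For a paired t-test with n = 93 the noncentrality is d·√93, and p is the two-sided 5% power from the noncentral t distribution on 92 degrees of freedom. The arms are independent, so:

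- P(significant in NG only) = p(1 − p)
- P(exactly one arm significant) = 2p(1 − p)

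| d (assumed) | d·√93 | p, each arm | NG only | Exactly one arm |
|---|---|---|---|---|
| 0.1 | 0.96 | 0.159 | 13% | 27% |
| 0.2 | 1.93 | 0.480 | 25% | 50% |
| 0.3 | 2.89 | 0.817 | 15% | 30% |
| 0.4 | 3.86 | 0.968 | 3% | 6% |
| 0.5 | 4.82 | 0.998 | 0.2% | 0.5% |

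A two-sided 5% between-arm test wrongly favours NG in 5%/2 = 2.5% of such trials.

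The NG-only error peaks near d = 0.2 and fades as d grows. The column for p shows why this does not make the paired test useful: at d of 0.4 to 0.5 it is significant in NG in about 97% to 99.8% of trials with no supplement effect.

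**3. What baseline adjustment gains.** Let r be the correlation between baseline and day-84 EQ-5D-5L, with equal variances at the two visits. The documents do not give r. Relative to an unadjusted day-84 comparison (variance 1), ANCOVA has variance 1 − r² and an unadjusted comparison of change has variance 2(1 − r).

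| r (assumed) | Day-84 value, unadjusted | Change, unadjusted | ANCOVA |
|---|---|---|---|
| 0.3 | 1 | 1.40 | 0.91 |
| 0.5 | 1 | 1.00 | 0.75 |
| 0.7 | 1 | 0.60 | 0.51 |

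ANCOVA has the smallest variance in every row, whichever unadjusted version the plan intends.

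**The case against.** The strongest objection is that the between-arm contrast is already in the plan. The sentence directly after the paired tests gives a t-test or Mann-Whitney test between groups, and continuous EQ-5D-5L is a quantitative variable, so it is covered. The aim and the sample size calculation both set PG against NG. This stands. A reader might infer from the primary outcome sentence that the continuous analysis is only before/after and cannot show a supplement effect. The documents do not support that reading.

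The sentence is also ambiguous: it may mean comparing the arms at each visit. That is possible, but on that reading the baseline comparison tests randomised groups before treatment. It also remains unsaid which of the listed tests carries the conclusion.

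Next, no section says that a significant result in NG but not in PG will count as evidence, and the Discussion states its expectation comparatively. This stands too. The percentages above show what that rule would cost if it were used. They are not the error rate of the plan as written.

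A further reply is that the choice of model is often left to an analysis plan or a fuller protocol. Silence on it would be no finding. Here, however, the article does name the tests, and they are unadjusted.

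Finally, one might add regression to the mean, because entry requires high fatigue. That selection acts on the fatigue score and reaches EQ-5D-5L only through a correlation the documents do not give. The point does not need it.

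**Conclusion.** The concern holds in a limited form. The primary outcome section describes the continuous EQ-5D-5L analysis by time point, and the Statistical analysis section offers within-arm and unadjusted between-arm tests at the same threshold without ranking them. Because both arms receive rehabilitation and are expected to improve, the within-arm tests cannot speak to the supplement. Using them for inference would give a false NG-only result in about 0.2% to 25% of trials over the assumed range of change, above the 2.5% benchmark at 0.1 to 0.4 SD (only marginally at 0.4) and below it at 0.5 SD.

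These figures assume 93 completers per arm, a paired t-test, equal true change in both arms and no supplement effect. The precision gain assumes r between 0.3 and 0.7. The powered responder comparison is between arms and is unaffected, so this is a matter of reconciling and improving the text, not a flaw that invalidates the trial.

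**What to change.** Reconcile the primary outcome and Statistical analysis sections as follows:

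- State that the inferential analysis of continuous EQ-5D-5L is the NG minus PG difference at day 84, adjusted for baseline EQ-5D-5L by ANCOVA, with a 95% CI. It replaces the unadjusted t or Mann-Whitney test for this outcome.
- Report within-arm change descriptively, for example as mean change with a 95% CI, without paired p-values.
- State that conclusions about the supplement rest only on the between-arm contrast.

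The cost is wording and one standard model. The baseline value is already collected, and sample size, visits and the powered responder comparison do not change.

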**Methods:**

ARACOV-2 study is a double-blind, parallel-group, randomized control trial with two parallel interventions: Nutritional supplement and telerehabilitation vs placebo supplement and telerehabilitation. The primary endpoint will be quality of life (EQ-5L-5D). The intervention will last 12 weeks with a daily intake of omega-3 or placebo and a daily supervised rehabilitation programme using telerehabilitation.

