#### Sample size calculation.

To estimate the sample size, a hypothesis test comparing the proportions of independent groups (PG vs. NG) assuming an alpha risk of 0.05 and a beta risk of 0.2 in a bilateral contrast requires 110 subjects in the placebo group and 110 subjects in the Nutritional supplement group to detect the difference in percentage of patients that will improve their EQ-5D-5L after intervention between the two groups, expected to be 30% and 50%, respectively, as statistically significant, and including a 15% loss estimated. Likewise, to assess the improvement in the pro inflammatory balance considering in this case the proportion of patients with change between pre-post intervention balances in each of the groups the estimated sample size will allow a difference of 20% or more between the two to be declared statistically significant, with a confidence level of 95% and a power of 80%. The estimation was carried out using the GRANMO sample size calculator, version 7.12 (Fig 3).

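### The primary outcome has two unranked analysis forms and no named EQ-5D-5L score, so the 0.05 alpha of the sample-size calculation does not cover the primary claim

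*Protocol article*

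**What the plan says.** - **Endpoint.** The Methods paragraph of the abstract names the instrument and no score: "The primary endpoint will be quality of life (EQ-5L-5D".
- **Components.** The Primary outcome section says of the EQ-5D-5L: "It consists of two components: the levels of severity by dimensions and a visual analogue scale (VAS) on general health".
- **Two analysis forms.** The same section gives a first form, "Quality of life will be analyzed as a continuous variable by comparing the relevant statistics according to their distribution", and joins to it a second, "as a qualitative variable by comparing the percentage of patients who improve their scores". It does not rank them, say which component each applies to, or define improvement.
- **Sample size.** One EQ-5D-5L hypothesis is sized, "assuming an alpha risk of 0.05 and a beta risk of 0.2 in a bilateral contrast", in order "to detect the difference in percentage of patients that will improve their EQ-5D-5L after intervention between the two groups". The expected percentages are 30% (placebo) and 50% (supplement), and 110 per group includes 15% loss. Which score must improve, and by how much, is not said.
- **Tests and level.** For continuous data between groups the Statistical analysis section plans "using the U Mann Whiney test for comparisons between groups and T-Student test for normal data"; dichotomous variables go to a chi-square test. On the level it says: "A significant level of 95% will be assumed (p <0.05". It gives no order and no split of alpha.
- **Limitations.** The Strengths and limitations section accepts that many contrasts at this level may raise the type I error. It offers no control and does not set the primary outcome apart.

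**The concern.** A primary outcome should lead to one test, or to a stated rule for combining several, so that the alpha used to size the trial is also the alpha of the main claim. Here one outcome carries two analyses on a two-component instrument, all judged at 0.05, and nothing says which result decides. The 5% risk in the sample-size statement belongs to one chi-square test. If the deciding version is chosen after the results are seen, the real risk of a false primary claim is higher than 5%, and no reader could show that the choice was independent of the data.

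This goes beyond detail that an article may leave to an analysis plan: the article itself assigns two forms to the primary outcome at one uncorrected level.

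**Working it through.** **1. Reproduce the plan's figure.** Inputs from the Sample size calculation section: p1 = 0.30, p2 = 0.50, two-sided alpha 0.05, power 0.80, loss 15%. With pooled variance, mean proportion 0.40 and no continuity correction:

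n = [1.960·√(2·0.40·0.60) + 0.842·√(0.30·0.70 + 0.50·0.50)]² / 0.20² = 93 per group

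93 / (1 − 0.15) = 109.4, rounded up to 110. This matches the article, so 110 per group is right for exactly one test at 0.05.

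**2. Ceiling if the tests were independent.** 1 − 0.95^k gives 9.75% for k = 2 and 18.5% for k = 4. The EQ-5D-5L analyses are correlated, so these are upper bounds only.

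**3. Correlated tests under the null.** Simulation with 93 per arm and 20,000 trials per setting. Change scores on two components are bivariate normal. Each score gets a t-test, and a chi-square test on the percent improved. The cut is set so that 30% improve, and each test counts at p<0.05. The article gives neither a correlation between components nor a cut, so both are assumed.

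| Correlation | One score, continuous or percent improved | Two scores, each both ways (four tests) |
|---|---|---|
| 0 | 8.3% | 15.8% |
| 0.3 | 8.7% | 15.6% |
| 0.5 | 8.3% | 14.9% |
| 0.7 | 8.0% | 13.5% |
| 0.9 | 8.4% | 12.1% |

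The correlation does not affect the one-score column; its spread is simulation noise. Each test alone stays near 5%. Percent improved alone, on either of two scores, gives about 8.5-10%.

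**4. Sensitivity to the cut.** With the cut set so that 50% improve (40,000 trials per setting), one score analysed both ways gives 7.5-7.7%. Four tests give 14.7% at correlation 0, falling to 11.2% at 0.9. Over both cuts the ranges are therefore about 8% and about 11-16%.

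**5. Cost of keeping several deciding tests.** With a Bonferroni split and the 30% v 50% contrast:
- Two tests (alpha 0.025): 113 evaluable, 113/0.85 = 132.9, so 133 per group. Power with 93 evaluable is 71%.
- Four tests (alpha 0.0125): 133 evaluable, 133/0.85 = 156.5, so 157 per group. Power with 93 evaluable is 61%.

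**The case against.** **The sample-size section already shows the intended test.** Percent improved is the only EQ-5D-5L hypothesis with an alpha, a power and an effect. This is good evidence of intent and should guide the fix. It does not close the gap: the Primary outcome section lists the continuous form first and ranks neither, and the score that must improve is still unnamed.

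**Four tests are not stated.** A reader might infer that each component is to be tested in each form. The article never says so and mentions no index or value set. Two forms are certain; four is a plausible extension, and the 11-16% depends on it.

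**No rule says that any positive version counts as success.** This is also correct. A reader might infer such a rule from the missing ranking, but none is written. The error rates above therefore apply only if either (or any) result could be claimed.

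**The continuous form may be a before-after comparison.** The sentence refers to the two time points, and the Statistical analysis section has separate within-group tests. On that reading the continuous form is not a second between-arm test. The wording allows both, which is a further reason to name the comparison.

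**An analysis plan may set the order, and the limitations disclose the problem.** A plan not shown may do so. Disclosure is not control, and the article's own text leaves the primary claim without a deciding test.

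**Conclusion.** The point holds in this form: two unranked analysis forms, an unnamed score and a uniform p<0.05 do not hold the primary claim at the alpha used to size the trial. The false-positive risk is about 8% if either form on one score could be claimed, and about 11-16% only if both components are also tested both ways. These figures rest on normal change scores, 93 evaluable per arm, correlations of 0 to 0.9, and a cut at which 30% to 50% improve.

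Two stronger readings are not supported. The 18.5% for four independent tests does not apply, because the tests are correlated and the count of four is inferred. The sample size is not wrong either: 110 per group is correct for the one test that it describes.

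**What to change.** Before unblinding, name one score, one analysis and one between-arm comparison at the day 84 visit as the deciding test.

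- **Choice consistent with the sample size:** percent improved on one named EQ-5D-5L score, with a stated definition of improvement, compared between arms by the planned chi-square test. This keeps 110 per group valid.
- **If a continuous between-arm difference is preferred:** name the score and state the power at 93 evaluable per arm. The article gives no mean difference or SD for any EQ-5D-5L score, so the present calculation would not support that choice.

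Label every other EQ-5D-5L analysis, including any within-group comparison, as secondary, and carry the same wording into the analysis plan and the registry entry.

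The cost is wording only, with no extra patients or visits. The downside is that a positive result on another version can no longer be called primary. Keeping several deciding tests would instead need 133 (two tests) or 157 (four tests) per group.
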